## Abstract

**Background:**

The emergence and spread of antibiotic resistant micro-organisms is a global concern, which is largely attributable to inaccurate prescribing of antibiotics to patients presenting with non-bacterial infections. The use of ‘omics’ technologies for discovery of novel infection related biomarkers combined with novel treatment algorithms offers possibilities for rapidly distinguishing between bacterial and viral infections. This distinction can be particularly important for patients suffering from lower respiratory tract infections (LRTI) and/or sepsis as they represent a significant burden to healthcare systems. Here we present the study details of the TAILORED-Treatment study, an observational, prospective, multi-centre study aiming to generate a multi-parametric model, combining host and pathogen data, for distinguishing between bacterial and viral aetiologies in children and adults with LRTI and/or sepsis.

**Methods:**

A total number of 1200 paediatric and adult patients aged 1 month and older with LRTI and/or sepsis or a non-infectious disease are recruited from Emergency Departments and hospital wards of seven Dutch and Israeli medical centres. A panel of three experienced physicians adjudicate a reference standard diagnosis for all patients (i.e., bacterial or viral infection) using all available clinical and laboratory information, including a 28-day follow-up assessment. Nasal swabs and blood samples are collected for multi-omics investigations including host RNA and protein biomarkers, nasal microbiota profiling, host genomic profiling and bacterial proteomics. Simplified data is entered into a custom-built database in order to develop a multi-parametric model and diagnostic tools for differentiating between bacterial and viral infections. The predictions from the model will be compared with the consensus diagnosis in order to determine its accuracy.

**Discussion:**

The TAILORED-Treatment study will provide new insights into the interplay between the host and micro-organisms. New host- or pathogen-related biomarkers will be used to generate a multi-parametric model for distinguishing between bacterial and viral infections. This model will be helpful to better guide antimicrobial therapy for patients with LRTI and sepsis. This study has the potential to improve patient care, reduce unnecessary antibiotic prescribing and will contribute positively to institutional, national and international healthcare economics.

**Trial Registration:**

NCT02025699. Registration Date: January, 1, 2014.

**Electronic supplementary material:**

The online version of this article (10.1186/s12879-018-3300-9) contains supplementary material, which is available to authorized users.

## Background

### The burden of antibiotic misuse

Antibiotics are the most prescribed class of drugs worldwide [1]. However, 30–50% of antibiotics are estimated to be prescribed inappropriately, making antibiotics also the most misused drug class [1–5]. Antibiotic overuse, i.e. prescribing antibiotics to treat a non-bacterial disease, is a serious problem. For example, in the US over 80 million antibiotic prescriptions are given annually for viral infections in the outpatient setting [6]. This may cause the emergence of adverse events (AEs) such as allergic reactions and antibiotic-associated diarrhoea [7]. Importantly, antibiotic overuse has been linked to the emergence of resistant strains of bacteria, by the Center for Disease Control considered as “one of the world’s most pressing health problems in the 21^st^ century” [8, 9]. Annually, 23,000 deaths due to resistant bacteria are expected in the US alone [8, 10]. Resistant bacteria are projected to cause over 10 M annual deaths worldwide by 2050, surpassing cancer as the leading cause of death [8, 11]. A second type of antibiotic misuse is underuse, i.e. delayed or no antibiotic treatment in case of a bacterial disease, from which a patient could have benefited [12–17]. Although reducing the risk of antibiotic-related AEs [18, 19], underuse of antibiotics may lead to a prolonged disease duration and an increased rate of complications that could have been avoided with early antimicrobial treatment [19–21]. For example, up to 15–40% of adult patients hospitalized for bacterial pneumonia in the US receive delayed or no antibiotic treatment [14, 15]. Finally, applying the wrong antibiotic spectrum to treat a bacterial disease is the third type of antibiotic misuse. For example, administering third generation cephalosporins instead of macrolides to treat a respiratory infection caused by atypical bacteria.

### Health economics consequences

Antibiotic overuse has also several health economics consequences. For instance, the annual cost of unnecessary antibiotic prescriptions for adult respiratory infections in the US is estimated to be $1.1 billion [22]. In addition, there are also indirect costs, including the costs of treating preventable antibiotic-related AEs and the costs of prolonged hospital stay as a result of AEs. Lastly, are the costs related to the emergence of antibiotic-resistant bacterial strains. The cost of treating patients with antibiotic-resistant bacteria is estimated at $16–26 billion annually in the US [23–25] and over €1.5 billion in the EU [26]. The health economics consequences of underuse of antibiotics include the costs of treating preventable complications and a prolonged disease duration resulting from a delayed or no antibiotic treatment [19–21].

### Antibiotics in respiratory tract infections and sepsis

Respiratory tract infections are one of the most common causes of hospital and outpatient visits in the EU, comprising 1 out of 3 admissions annually [9]. In patients with mild respiratory tract infections, over prescription of antibiotics in general and prescription of broad spectrum antibiotics are large problems. Broad spectrum antibiotics account for approximately half of all antibiotic prescribing for children with acute RTI [27], with the above mentioned consequences [8]. Sepsis-related hospital admissions are less frequent but represent a significant burden to healthcare systems in terms of adverse patient outcomes and the need for rapid, but effective, intervention strategies [28]. In septic patients the key clinical challenge is to ensure that the correct antimicrobial treatment is administered, and that this therapy is administered as soon as possible [29].

### Limitations of current diagnostic tools

Although the current diagnostic tools for facilitating appropriate use of antibiotics (such as culture-, PCR-, and immunoassay-based) may be valuable in some clinical situations, they have major limitations (Fig. 1). First, existing diagnostic tools often require hours to days to provide information, whereas physicians need to decide whether to prescribe antibiotics within shorter time periods. Second, available diagnostic technologies usually require direct sampling of the pathogen. Such sampling is often not feasible if the infection site is inaccessible (e.g., pneumonia, sinusitis, middle-ear infection, etc.). A third limitation is that available technologies usually search for the presence of specific bacteria or viruses. However, many types of bacteria and viruses could be present as part of the natural flora without causing an infection. For example, the important respiratory tract pathogenic bacteria *S. pneumoniae* is also part of the upper respiratory tract natural flora in up to 68% and 15% of healthy children and adults, respectively [30] and respiratory viruses were detected in 35.4% of a-symptomatic children [31]. Finally, diagnostic solutions that were developed for detection of a specific pathogenic strain, often fail to detect the constantly evolving and emerging strains of the same family of pathogens, for example rapid Influenza tests showed low sensitivity, 45%, during the 2009 H1N1 influenza A viral outbreak [32]. These limitations lead to a ‘diagnostic gap’, which in turn often leads physicians to either over-prescribe (e.g., ‘just-in-case’ approach) or under-prescribe (e.g., ‘watchful waiting’ approach) antibiotics [18–20], both of which adversely influence patient care and health economics.

**Fig. 1 Fig1:**
[figure not shown]
Limitations of current diagnostic tools

### The TAILORED-treatment project

The health and health economics consequences of antibiotic misuse highlight the need for a diagnostic tool that would help physicians to use antibiotics appropriately. Ideally, this diagnostic tool should provide a diagnosis that can accurately and rapidly differentiate between bacterial and viral infections. However, as previously described, current diagnostic tools are often inadequate (Fig. 1). Therefore, the TAILORED-Treatment consortium was established to develop new tools aimed at increasing the effectiveness of antibiotic therapy, reduce adverse events, and limit the emergence of antimicrobial resistance in children and adults. In reality, targeted antimicrobial therapy can most effectively be achieved by utilizing personalized data to facilitate a tailored and optimized approach to individual patient treatment. This can best be achieved by utilizing knowledge gained from both host-centred and pathogen-centred parameters during health and disease. Unfortunately, these parameters have traditionally, tended to be measured independently, and used on an ad hoc basis without careful integration for the best treatment of the patient. However, recent advances in the development of high-throughput and sensitive molecular-based technologies, improved databases, and bioinformatics analysis tools, rapidly enabling that the goal of personalized medicine and treatment can be reached. Unfortunately, however, there currently exists a ‘technological gap’ between recent state-of-the-art methodologies (for example with respect to gaining new insights into novel host-pathogen interactions) and laboratory-to-bedside results to benefit patients, physicians and society as a whole [33]. The observational TAILORED-Treatment project is designed to bridge this technological gap in order to generate novel insights and innovations that are readily exploitable in the field of personalized medicine and infectious diseases.

### Study objectives

#### Primary objective

To develop a novel multi-parametric diagnostic model for the management of patients with LRTI and/or sepsis that is based on novel pathogen- and host-related factors.

#### Secondary objectives

Identify individual as well as sets of blood host biomarkers for differentiating between bacterial, and viral aetiologies and determine the sensitivity and specificity of these biomarkers in distinguishing between the different infection types;Identify individual as well as sets of blood host biomarkers for differentiating between bacterial subtypes, namely Gram positive, Gram negative and atypical bacteria;Characterize the temporal dynamics of the host-pathogen interactions based on multiple sampling before and during antimicrobial treatment;Characterize the respiratory microbiome in patients presenting with LRTI and/or sepsis;Develop a mass spectrometry based, rapid detection technique for identification of microbial pathogens and antimicrobial resistances in clinical samples;Develop a personalized treatment algorithm for tailored antimicrobial therapy that integrates clinical, molecular and biochemical data;Define genetic mechanisms underlying the differential host response between patients with viral versus bacterial infection.

## Methods

### General study design

In this prospective, multi-centre, observational study, an expected total number of 1200 paediatric and adult patients aged 1 month and older with suspected LRTI and/or sepsis or a non-infectious disease are recruited, in order to develop a diagnostic model to differentiate between bacterial and viral infections. The study will generate a model for patients with LRTI and a separate model for patients with sepsis. The prediction of the model obtained from each patient will be compared with a consensus diagnosis by a panel of three experts in order to determine its accuracy (Fig. 2). The study is a non-interventional study, and therefore, the diagnostic prediction of the model will not be used for any clinical or diagnostics decision making. Local data monitor plans were used and executed by local, independent monitors.

**Fig. 2 Fig2:**
[figure not shown]
Schematic diagram of the study workflow

### Study participants

Patients aged 1 month and older that attend the Emergency Department (ED) and hospital wards of seven Dutch and Israel medical centres (secondary and tertiary) due to a suspected LRTI and/or sepsis that agree (or their legal guardians agrees) to sign an informed consent and meet the inclusion criteria and none of the exclusion criteria (Table 1), are eligible to participate in the study. Informed consent is asked by the study team (i.e. research nurses or medical doctor). Sepsis criteria are defined according to published criteria [34]. Patients receive care as usual. The non-infectious disease group include patients with clinical signs of a non-infectious disease.

**Table 1 Tab1:** Eligible criteria for Tailored Treatment study

Inclusion criteria	Exclusion criteria
Age ≥ 1 month	Proven or suspected HIV, HBV, or HCV infection
Symptoms ≤8 days	Post-transplant
*LRTI; ≥ 2 signs*	Congenital immune deficiency
Respiratory rate > 20/min^a^	Obvious alternative causes of respiratory distress
Chest cough	Nosocomial LRTI (> 3 days after hospitalization)
Nasal flaring	Other febrile infection during the past 3 weeks
Retractions	Active (haematological) malignancy
Rales	Immune-suppressive or immune-modulating therapies
Expiratory wheeze	Moderate to severe psychomotor retardation
Decreased breath sounds	Moderate to severe congenital metabolic disorder
*Sepsis* ^b^ *; ≥ 2 signs* ^c^	
Heartrate > 90/min	
Respiratory rate > 20/min	
Core body temperature > 38 °C or < 36 °C	
White blood cell count > 12,000 cells/ μl or < 4000/ μl	

^a^WHO age-specific criteria for tachypnea will be used for children [41]

^b^Age-specific criteria for sepsis criteria according to the guidelines of the International Paediatric Sepsis Consensus Conference 2005 will be used for children [42]

^c^One of which must be abnormal temperature or white blood cell count

*HIV* human immunodeficiency virus, *HBV* hepatitis B virus, *HCV* hepatitis C virus

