#### Sample collection

For study purposes two blood samples, two nasal swabs and (in case of diarrhoea) a stool sample are collected (Fig. 2). Blood and nasal swabs sampling at two sampling points (at inclusion and after 3–5 days) is performed in hospitalized Dutch children in order to monitor the temporal dynamics of the host-pathogen interactions. One nasal swab sample (Universal Transport Medium, Copan, USA) is used for PCR based microbiological investigations performed for the establishment of patient diagnosis (only at inclusion). The PCR results are included in the eCRF and are available to the TAILORED-Treatment expert panel while determining the diagnosis of the patient (Fig. 2). The second nasal swab is collected in Transport Medium suitable for bacterial culturing (e-swab, Liquid Amies Medium, Copan), this sample is used for respiratory microbiome investigations and to develop a rapid detection technique for identification of microbial pathogens and antimicrobial resistances, based on mass spectrometry and proteomics for discovery of peptide biomarkers. Serum samples are used for different proteomic measurements, leukocytes are isolated for discovery of RNA-based biomarkers. Following RNA isolation, remaining DNA is used for GWAS studies. GWAS analyses is performed in the Netherlands, as Institutional review board (IRB) approval for genetic testing is not obtained in Israel. DNA collection is mentioned explicitly in the patient information. Blood samples are collected from children with a non-infectious disease only if blood sampling is required as part of their routine care. In cases of diarrhoea on enrolment, stool samples are collected. These samples will be evaluated to identify *Clostridium difficile* infections.

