## Discussion and expected results

The inappropriate use of antibiotics has severe global health and economic consequences, including the emergence of antibiotic-resistant bacteria [33]. A major driver of antibiotic misuse is the inability to accurately distinguish between bacterial and viral infections based on currently available diagnostic solutions [33]. Many different biomarkers have been investigated in previous studies, none of them being accurate enough to establish or rule out bacterial infections [40]. The TAILORED-Treatment study is a novel collaboration between (university) hospitals, academic institutions and (diagnostic) industry, aimed to collect and analyse ‘multi-omics’ data from patients suffering from LRTI and/or sepsis. Univariate and multivariate analysis of the data will generate new biomarkers to distinguish between bacterial, viral, and non-infectious disease. The multi-omics approach to generate infectious disease algorithms utilised by this study is currently unique within this area of medicine and provides a template for follow-up combined infectious disease data studies in the future.

Some challenges remain for this type of study. First of all, as described previously, in a subset of patients, sampling of blood and nasal swabs at two sampling points (at presentation and after 3–5 days) should allow to measure data on the temporal dynamics of the host-pathogen interaction. However, if patients are not admitted to the hospital or are already discharged after 1 or 2 days, it is hard to collect a second sample. However, consecutive samples are not necessarily needed in order to achieve the primary objective. A second challenge is how to best interpret and efficiently act on the wealth of data available. Therefore, dedicated bioinformatics professionals are part of the TAILORED-Treatment consortium, for building the unique (HoPOIT) database and to develop the treatment algorithms. Finally, the study is a non-interventional study, and therefore, the diagnostic prediction of the model is not used for any clinical, diagnostic or prognostic decision making. After completing the study, utility studies will be needed to establish the clinical impact of any TAILORED-Treatment algorithms developed.

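### Patients may be sampled after antibiotics have started, and accuracy is pooled over exposure, so it may differ from accuracy at the prescribing decision

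*Protocol article*

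**What the plan says.** All references are to the protocol article.

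- **Who enters.** Study participants recruits "Patients aged 1 month and older that attend the Emergency Department (ED) and hospital wards of seven Dutch and Israel medical centres", for suspected LRTI and/or sepsis. Table 1 sets one general time limit, "Symptoms ≤8 days". None of its ten exclusions concerns antibiotics. The only one that refers to time in hospital is "Nosocomial LRTI (> 3 days after hospitalization"; it names LRTI and not sepsis.
- **Treatment.** "Patients receive care as usual".
- **When samples are taken.** Under Sample collection, "Blood and nasal swabs sampling at two sampling points (at inclusion and after 3–5 days) is performed in hospitalized Dutch children". The Discussion describes the serially sampled subset differently: "sampling of blood and nasal swabs at two sampling points (at presentation and after 3–5 days". One secondary objective, on temporal dynamics, expects samples both before treatment and while it is given.
- **What is measured.** One nasal swab serves the microbiome and proteomic work ("this sample is used for respiratory microbiome investigations and to develop a rapid detection technique for identification of microbial pathogens and antimicrobial resistances"); blood supplies the host protein and RNA markers.
- **Intended use.** The Background faults current tools because "physicians need to decide whether to prescribe antibiotics within shorter time periods". The Abstract expects the model to help guide antimicrobial therapy.
- **Accuracy.** The section on computing accuracy compares the model's classification with the consensus diagnosis. It mentions neither antibiotic exposure nor time of sampling.

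**The concern.** A patient sampled on a ward after antibiotics have begun is already past the decision to start them. Under usual care, antibiotics go more readily to patients thought to have a bacterial infection, so exposure at sampling is likely to differ between the two classes the model must separate. If exposure also changes nasal flora, bacterial peptides or blood markers, two things can follow. The Stage A model may partly use the effects of treatment as a signal for class. Stage B, for which no different entry rule is stated, would then carry the same signal and would not expose it in a pooled analysis. At stake is whether the reported sensitivity and specificity apply to the untreated patient for whom the start of antibiotics is still open.

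**Working it through.** **1. What the text permits.** Set side by side, the passages allow this sequence: symptoms begin, the patient is admitted and treated under usual care, and is then enrolled from the ward within 8 days of onset and sampled at inclusion. No printed criterion stops it. The nosocomial exclusion concerns where an LRTI began, not how late a community-onset case is enrolled. The phrases that point to early sampling (the secondary objective and the Discussion) both describe serial sampling, which Sample collection confines to hospitalized Dutch children, and neither is worded as a rule.

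**2. The plan's own figures.** The document gives no share of patients treated before sampling, so there is no figure to reproduce on this point. The sample-size section supplies a reference: null sensitivity 70%, alternative 90%, one-sided α = 0.01, power 80%, n ≤ 76 bacterial patients. The printed formula gives 43.46, so 44. Thus 76 is a loose upper bound, with normal-approximation power of 98.8%. That discrepancy is a separate matter; here it only shows the room available for stratifying.

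**3. Effect of pooling.** Let f be the share of a class sampled after the first dose, and S_pre and S_post the sensitivities before and after it:

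pooled = (1 − f)·S_pre + f·S_post, so the shift from S_pre is f·(S_post − S_pre).

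All values of f and S below are assumptions.

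- Range: 0.20 × 5 = 1 point; 0.60 × 15 = 9 points, in either direction.
- Upward: S_pre 70%, S_post 95%. With f = 30%, 0.7 × 70 + 0.3 × 95 = 77.5%. With f = 50%, 82.5%.
- Downward: S_pre 90%, S_post 60%, f = 30%: 0.7 × 90 + 0.3 × 60 = 81%.

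With 76 cases, the exact one-sided 1% test rejects 70% when at least 63 are classified correctly. The chance of rejection is 16.1% and 53.7% in the two upward cases, against 0.8% if sensitivity is 70% throughout. In the downward case it is 40.3%, against 98.2% if sensitivity is 90% throughout. The same formula holds for specificity with the viral class's own f. As f probably differs by class, the two measures need not shift alike.

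**4. Cost of stratifying.** If 40% of the 76 were sampled after treatment, about 46 would remain, with 83.3% power for 90% against 70%. At 50%, 38 would remain, with 71.1%. Stage B alone is smaller. If it holds 300 of 1200 patients and a proportional share of the 76, it has 300/1200 × 76 = 19 paediatric bacterial consensus cases. At 40% treated, 0.6 × 19 ≈ 11 are pre-dose. At 90% sensitivity the approximate 95% half-width, 1.96·√(0.9 × 0.1/n), grows from 13.5 points (n = 19) to 17.7 points (n = 11).

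**The case against.** The strongest reply is that this is a condensed article. A sampling window, a first-dose time on the case record form and an analysis by exposure may stand in documents not shown. Follow-up already collects total antibiotic use. That is a fair limit on confidence. It does not remove the point, because the article prints its eligibility table and its sampling times, and these do not agree on when the first sample falls.

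Second, the sponsor evidently wants early samples: the temporal-dynamics objective and the Discussion both say so, and ED patients may well be sampled untreated. This stands, and it rules out reading the plan as one that knowingly samples after treatment.

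Third, the primary objective concerns management of LRTI and sepsis in general. Choice of spectrum and tailored therapy can matter after a first dose, so including treated patients is a defensible choice of population. This also stands. A reader might infer that the primary objective goes unanswered; the text does not support that. Only a claim about starting antibiotics needs the pre-dose patients.

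Fourth, entry is for patients who attend because of suspected infection, which may already keep out sepsis that arises in hospital. So one cannot say that such sepsis qualifies on any day. But the same reading would make the printed nosocomial LRTI exclusion unnecessary, so the question stays open for sepsis.

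**Conclusion.** The point holds as a gap between what the printed entry and sampling rules permit and the use for which accuracy will be quoted. Treated patients can enter, exposure is likely to be associated with class, and the accuracy analysis as described does not separate them.

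A reader might go further and conclude that reported accuracy will be inflated by some number of points. The documents do not support that. They give neither the treated share nor the difference in accuracy, and the shift can go either way. The 1–9 points are an illustration on assumed inputs, not an estimate. The conclusion also rests on the assumption that antibiotics under usual care follow clinical suspicion and that they may alter the measured inputs; the article states neither. Confidence is medium, because fuller study documents may already settle the timing.

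**What to change.** 1. Use the time of the first antibiotic dose from any source, relative to the inclusion sample. Patients with no dose before sampling count as pre-dose.
2. Report Stage B sensitivity and specificity separately for patients sampled before and after the first dose. Rest any claim about guiding the start of antibiotics on the pre-dose stratum.
3. Account for exposure in Stage A modelling, at least as a sensitivity analysis. Fitting on pre-dose samples only is possible, but it trades training data for a cleaner population and need not be the default.
4. Report any hospital-onset sepsis separately in the sepsis model, since the nosocomial exclusion names only LRTI.
5. Reconcile the secondary objective on temporal dynamics, Study participants, Sample collection and the Discussion on when the first sample is taken.

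The cost is one time variable, if it is not already recorded, and a stratified table. Clinical care is unchanged. The downside is wider intervals in the pre-dose stratum, felt most in Stage B.
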